## Abstract

**Background:**

Leprosy is a chronic, granulomatous, and infectious disease caused by *Mycobacterium leprae* and *Mycobacterium lepromatosis.* The diagnosis of the disease is primarily clinical based on the observation of the characteristic signs and symptoms. Laboratory tests such as bacilloscopy and skin biopsy can also be used to aid in diagnosis. Due to the lack of complementary tests with 100% sensitivity, diagnosis is often made based on the combination of clinical, laboratory, and molecular criteria. Although *M leprae* has a tropism for nerves, no validated minimally invasive procedure exists to sample nerves for this disease. The investigation of the genetic material of the etiological agents that cause leprosy through perineural collection guided by ultrasound is a promising method for improving diagnostic accuracy.

**Objective:**

This study aims to evaluate the accuracy of ultrasound-guided perineural aspirate in the diagnosis of leprosy. The World Health Organization leprosy composite reference standard will be used as the benchmark for diagnostic accuracy. We will also perform the clinical, molecular, and ultrasonographic follow-up of patients. The study will be performed at the University Hospital of Brasília, a reference center for the treatment of leprosy in the central-west region of Brazil.

**Methods:**

This will be a diagnostic study with consecutive prospective recruitment of patients referred to the leprosy outpatient clinic of University Hospital of Brasília for diagnosis and treatment. During follow-up, clinical and molecular examinations will be performed, and their results will be compared to the sonographic findings, which will be collected monthly for 1 year. Patients will be evaluated clinically, via ultrasound, and molecularly in 2 stages of leprosy diagnosis and treatment: immediately after clinical diagnosis and 1 year after the start of treatment. Subcutaneous aspiration of the ulnar nerve will be performed in the ulnar tunnel guided by ultrasound. The aspirated material will be used for identification of bacillary DNA and RNA at the time of diagnosis and 1 year after the start of treatment.

**Results:**

Grant funding for this study was received in May 2023, August 2023, and June 2026. As of October 2025, no patients have been enrolled in this study. Patient recruitment started in January 2026 and is expected to be concluded in December 2026. Collection of clinical and laboratorial data will follow the same schedule as that of recruitment. Analysis of the collected data will be conducted between February 2027 and July 2027, with results expected to be submitted to publication by August 2027.

**Conclusions:**

We believe that ultrasound-guided perineural aspirate will increase the accuracy of leprosy diagnosis and may demonstrate the viability of the bacillus before and after treatment via RNA identification.

**International Registered Report Identifier (IRRID):**

PRR1-10.2196/86421

## Introduction

### Background

Leprosy is a disease that has chronic, granulomatous, and infectious-contagious characteristics. It is caused by *Mycobacterium leprae* or *Mycobacterium lepromatosis*, which are gram-positive and acidic-resistant bacilli that have neural tropism. The disease usually affects superficial nerves of the skin and peripheral nerves. It can affect the eyes; other organs such as the liver, spleen, and testicles; and mucus and bone marrow [1]. When untreated, it evolves slowly and gradually, and its sequelae may result in physical disabilities and deformities [2-4].

The Global Leprosy Strategy 2021-2030 aims to eradicate leprosy and is part of the action plan for neglected tropical diseases [5]. One of the major challenges in the elimination and prevention of sequelae is the absence of a standard test with high sensitivity and specificity for all forms of the disease [6]. After infection, *M leprae* is preferentially concentrated in the skin and neural tissue, and neurological involvement may occur before diagnosis and constitute the only symptom of the disease [7]. Routine methods allow for the collection of cutaneous biological material for the detection of this mycobacterium. However, the collection of neural material is limited by the need to use invasive methods that can potentially lead to neurological sequelae [8].

Although special histopathological stains are routinely used to detect the mycobacterium in standard laboratories [9], molecular biology methods such as polymerase chain reaction (PCR) have greater sensitivity for diagnosis, and their incorporation into the diagnostic routine will potentially allow for earlier diagnosis with the prevention of sequelae [10-13]. The *M leprae*–specific repetitive element (RLEP) is the most commonly used target for this reaction, being also suggested to be the most sensitive and specific [13,14]. PCR also allows for measures of parasite viability that are useful in the evaluation of therapeutic response and possible drug resistance [15].

Clinically, the evaluation of possible nervous involvement is conducted via neurological examination in search of sensorimotor deficit and through palpation of nerves to evaluate nervous thickening [16]. In the appropriate clinical context, the presence of signs of peripheral neuropathy is often diagnostic for leprosy. The time when neurological deficit has already developed constitutes a very late stage for diagnosis, resulting in irreversible sequelae [17]. In addition, peripheral nerve palpation is examiner dependent and has low accuracy in the diagnosis of the disease [18].

Ultrasound has higher spatial resolution when compared with magnetic resonance imaging, which results in higher sensitivity with equivalent specificity to detect focal peripheral nerve pathology [19]. It is a noninvasive and low-cost method that provides real-time and dynamic examination, enabling the acquisition of accurate morphological information (diameter and fascicular abnormalities) without side effects for the patient. Through the Doppler mode, it is also possible to know whether there is an increase in local vascular flow indicating an inflammatory process [20,21]. Additionally, the test is also used for therapeutic procedures and for the collection of biological material in a minimally invasive way [22]. We hypothesize that minimally invasive perineural aspiration by means of high-frequency ultrasonography is feasible and that PCR performed in the aspirate will be accurate to diagnose leprosy. As the neural sequelae related to leprosy greatly impact the quality of life of patients, it is essential to improve diagnosis with a focus on neural involvement. We believe that the association of ultrasonography with minimally invasive techniques for peripheral nerve assessment is an interesting strategy to achieve this goal.

### Rationale for the Study

The diagnosis of leprosy is primarily clinical and epidemiological [2-4]. However, there are significant challenges in the current diagnostic practice. As a result of the long incubation period and changes in household contacts, complete epidemiological investigation can be difficult. Additionally, clinical examination, which includes dermato-neurological analysis identifying lesions or areas of skin with altered sensitivity and palpation to identify nerve thickening, is operator dependent and has been shown to have low agreement even among trained personnel [23].

In addition to essential clinical analysis, detection of the bacillus through microscopic examination (slit skin smear [SSS] microscopy or biopsy) confirms the diagnosis. However, the sensitivity of these tests is less than 50% due to the latency of the bacillus in nonaccessible perineural structures [24,25].

The literature shows that ultrasonography provides objective morphological data in the neural evaluation of patients with leprosy [20]. In this way, the use of ultrasound examinations aims to help in the early diagnosis of the disease, improving patients’ prognosis and reducing disease transmissibility. Additionally, it is an excellent adjunct technique to guide procedures such as perineural aspirate [26-31].

The general objective of this study is to perform clinical, molecular, and ultrasonographic follow-up of patients with leprosy treated at the University Hospital of Brasília (UHB), aiming at better accuracy of the diagnosis of leprosy. Specific objectives are to (1) evaluate the diagnostic and prognostic accuracy of clinical, molecular, and ultrasound scores in leprosy; (2) compare the analysis of the ultrasound image with the clinical evaluation of the patient with suspected leprosy; and (3) create a biorepository of DNA and complementary DNA (cDNA) samples to carry out laboratory research aimed at clarifying pathological and molecular aspects related to disease activity, with a view to develop effective early treatment for affected patients.

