## Methods

### Study Design and Population Studied

This is a diagnostic study with prospective collection. Patients aged 14 years or older will be enrolled after agreeing to and signing the informed consent form. The informed consent form will be signed by the responsible adult in the case of participants under 18 years of age. This research is in line with the Declaration of Helsinki and its revision made in 2013.

The case definition will be determined by a professional external to the investigation according to the standard procedures of the leprosy outpatient clinic of the UHB, which consist of clinical history, general physical examination, and dermato-neurological examination. Case definition will follow the World Health Organization (WHO) composite reference standard for the diagnosis of leprosy [32]. Direct investigation of the bacillus will be performed via SSSs of lesions, earlobes, and elbows. After the procedure, collected material from perineural aspiration and dermal lesions will be sent to the laboratory within a maximum period of 24 hours. The results of the perineural aspiration will only be known to researchers by the end of the study. Morphological data described in the ultrasound examination will be accessed by a blinded ultrasound specialist based on deidentified ultrasound images.

Clinical and molecular examinations will be performed, and their results will be compared to the sonographic findings, which will be collected monthly for 1 year. Molecular findings will be compared to the composite reference standard. Patients will be evaluated clinically, via ultrasound, and molecularly immediately after clinical diagnosis and 1 year after the start of treatment.

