### Clinical Data

The following clinical and complementary variables will be collected: age, sex, place of residence, occupation, history of household or close contact with a leprosy case, duration of symptoms, type of presenting symptoms (eg, sensory loss, paresthesia, pain, or muscle weakness), number and anatomical distribution of skin lesions, morphological characteristics of lesions (hypopigmented, erythematous, infiltrated, or nodular), presence of sensory loss within skin lesions, presence of peripheral nerve thickening on physical examination, nerves affected, sensory impairment on neurological examination, motor impairment, disability grade at diagnosis according to the WHO criteria, clinical classification of leprosy, operational classification according to WHO criteria (paucibacillary or multi-bacillary), and classification according to the Ridley-Jopling spectrum (indeterminate, tuberculoid, borderline tuberculoid, midborderline, borderline lepromatous, and lepromatous). Complementary diagnostic data will include SSS results and bacillary index when available, as well as histopathological findings from skin or nerve biopsy when performed. A standardized simplified neurological examination according to Brazil’s Ministry of Health guidelines will be conducted for all patients [33]. Table 1 aggregates all variables to be collected, and Figure 1 summarizes the study timeline.

**Table 1 table1:** Variables to be collected.

Category	Variables
Participant characteristics	Age, sex, place of residence, occupation, and history of household or close contact with a leprosy case
Clinical and disease characteristics	Duration of symptoms, type of presenting symptoms (sensory loss, paresthesia, pain, and muscle weakness), number of skin lesions, anatomical distribution of skin lesions, morphology of lesions (hypopigmented, erythematous, infiltrated, and nodular), sensory loss within lesions, peripheral nerve thickening on physical examination, nerves affected, sensory impairment on neurological examination, motor impairment, disability grade at diagnosis (WHO^a^ criteria), clinical classification of leprosy, operational classification (paucibacillary or multi-bacillary), Ridley-Jopling classification (indeterminate, tuberculoid, borderline tuberculoid, midborderline, borderline lepromatous, and lepromatous), and simplified neurological examination according to Brazilian Ministry of Health guidelines

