Conventional diagnostic tests	Slit skin smear results, bacillary index, and histopathological findings from skin or nerve biopsy (when performed)
Index test—PCR^b^ from perineural aspirate	PCR detection of Mycobacterium leprae targets: RLEP, sodA, and 16S rRNA^c^
Complementary diagnostic test—ultrasound examination	Nerves evaluated: median nerve (carpal tunnel and pronator quadratus), ulnar nerve (ulnar tunnel, immediately before the ulnar tunnel, Guyon canal, and immediately before the Guyon canal), common fibular nerve (fibular head), and tibial nerve (tarsal tunnel and 4 cm above the tarsal tunnel); CSA^d^ measurements; asymmetry indexes (change in CSA^e^ and CSA ratio); focality indexes (change in TPT^f^ and TPT ratio); intraneural or epineural Doppler signal (hypervascularity); nerve echogenicity (normal or abnormal); loss of fascicular pattern; and focal nerve thickening
Reference standard (composite clinical diagnosis)	Presence of ≥1 cardinal sign of leprosy: (1) definite sensory loss in a hypopigmented or reddish skin lesion, (2) thickened or enlarged peripheral nerve with sensory loss and/or muscle weakness, and (3) acid-fast bacilli in slit skin smear

^a^WHO: World Health Organization.

^b^PCR: polymerase chain reaction. PCR targets: RLEP, sodA, and 16S ribosomal RNA of *M leprae*.

^c^rRNA: ribosomal RNA.

^d^CSA: cross-sectional area of the nerve.

^e^Absolute difference between contralateral nerves.

^f^TPT: difference between the thickest and thinnest points along the nerve.

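### Objective 1 asks for the diagnostic accuracy of a clinical score, but the only named benchmark is built largely from clinical signs, so a score containing those signs would be inflated by incorporation

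*Protocol article*

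**What the plan says.** In the protocol article, the section Rationale for the Study sets as the first specific objective to "evaluate the diagnostic and prognostic accuracy of clinical, molecular, and ultrasound scores in leprosy". The three kinds of score are listed side by side.

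The Objective paragraph of the abstract names the benchmark: "The World Health Organization leprosy composite reference standard will be used as the benchmark for diagnostic accuracy". Table 1 (under Clinical Data) defines it as "Presence of ≥1 cardinal sign of leprosy: (1) definite sensory loss in a hypopigmented or reddish skin lesion", or "thickened or enlarged peripheral nerve with sensory loss and/or muscle weakness", or "acid-fast bacilli in slit skin smear". Study Design and Population Studied says the case definition follows the clinic's standard procedures, "which consist of clinical history, general physical examination, and dermato-neurological examination", with smears taken as well.

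The clinical variables in the same Table 1 include "sensory loss within lesions, peripheral nerve thickening on physical examination, nerves affected, sensory impairment on neurological examination, motor impairment".

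The section Case Definition: Composite Reference Standard states that ultrasound and PCR on the aspirate play no part in allocating patients to the leprosy or nonleprosy group. It makes no corresponding statement about a clinical score. The section Diagnostic Accuracy gives measures for PCR and for quantitative ultrasound variables, and none for a clinical score.

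**The concern.** A test should not be judged against a reference that already contains it. Two of the three ways to be classed as leprosy are findings of the clinical examination, and the same findings are available as ingredients of a clinical score. A score that uses them agrees with the reference partly because it is part of the reference, whatever the signs say about true disease. This is incorporation bias.

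What is at stake is the comparison that objective 1 invites. The molecular and ultrasound scores are protected from this bias and the clinical score is not. Reported together, the clinical score could look as good as or better than the other two for reasons of construction, and a reader could conclude that PCR or ultrasound adds little. That would sit badly with the article's own premise, in the Rationale, that clinical examination depends on the operator and shows low agreement even among trained staff.

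**Working it through.** The plan gives no accuracy figure for a clinical score, so there is none to reproduce. The check asks how large an AUC the construction alone can produce.

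**Inputs from the article**
- Leprosy in half of referred patients; 54 patients per group (Sample Calculation).
- Smear positive in 50% of cases (Sample Calculation), or in about 30%, since Expected Findings puts negatives at about 70%.
- Smear-positive share of the whole cohort, *s*: 0.50 × 0.50 = 0.25, or 0.30 × 0.50 = 0.15. The value *s* = 0 is added as the limiting case.

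**Assumptions, not from the article**
- The score uses the two clinical cardinal signs, taken from the same examination as the reference.
- The two signs are equally frequent. Signs and smear are independent of each other and of true disease, so the signs carry no diagnostic information.
- The composite is positive in 50% of patients.

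**Step 1: bounds without simulation.** Take the rule: positive if sign 1 or sign 2 is present. Every rule-positive patient is reference-positive, so specificity = 54/54 = 100%. Sensitivity is lost only through patients positive on smear alone. With smear sensitivity of 50% these are at most half of the reference-positive patients, so sensitivity is 50% to 100%. Overall accuracy runs from (27 + 54)/108 = 75% to 108/108 = 100%.

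**Step 2: uninformative signs.** Let *u* be the probability of at least one clinical sign. From (1 − *u*)(1 − *s*) = 0.5, *u* = 1 − 0.5/(1 − *s*). Sensitivity = *u*/0.5. All reference-negative patients score zero, so for the count of signs AUC = sensitivity + (1 − sensitivity)/2.

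| *s* | *u* | Sensitivity | Specificity | AUC against composite | AUC against true disease |
|---|---|---|---|---|---|
| 0 | 0.500 | 1.00 | 1.00 | 1.00 | 0.50 |
| 0.15 | 0.412 | 0.82 | 1.00 | 0.91 | 0.50 |
| 0.25 | 0.333 | 0.67 | 1.00 | 0.83 | 0.50 |

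A simulation of 1,000,000 patients gave the same values.

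**Step 3: diluted score.** Add three irrelevant items, each positive with probability 0.5. The difference between two patients' noise totals runs from −3 to 3 with weights 1, 6, 15, 20, 15, 6, 1 over 64. A patient with one sign then outranks a patient with none with probability (42 + 7.5)/64 = 0.773; with two signs, (57 + 3)/64 = 0.938; with none, 0.5. Weighting by the shares of reference-positive patients with one, two and no signs:
- *s* = 0: 0.829 × 0.773 + 0.172 × 0.938 = 0.80
- *s* = 0.15: 0.715 × 0.773 + 0.109 × 0.938 + 0.176 × 0.5 = 0.74
- *s* = 0.25: 0.599 × 0.773 + 0.067 × 0.938 + 0.333 × 0.5 = 0.69

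The noise items alone give 0.50. Everything above that comes from the shared signs.

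**The case against.** The strongest reply is that the article does not plan this analysis. Study Design and Population Studied compares molecular findings with the composite and compares clinical results with sonographic ones. Diagnostic Accuracy covers PCR and ultrasound only. Table 1 labels PCR the index test and ultrasound the complementary test. The score is undefined, which an article may leave to the full protocol, and Table 1 lists many items outside the composite, such as contact history and duration of symptoms. Objective 1 also covers prognosis, where disability grade and disease class fit naturally. All of this stands, and it makes the point smaller and conditional.

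A reader might also infer that any clinical score must have 100% specificity, or that the clinical part of the objective cannot fail. The documents do not support that. Sign 2 needs a thickened nerve together with a deficit, while the clinical variables record thickening, sensory loss and weakness separately, so a score counting single items can be positive without a cardinal sign. The reference is assigned by a professional external to the investigation, and the text leaves open whether the study's clinical data come from a second examination. If they do, discordance is possible, although the score would then largely measure agreement between examiners on the same signs. The diluted score at 0.69 shows that the inflation has limits.

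These replies do not remove the conflict: objective 1 still promises diagnostic accuracy for a clinical score, and no benchmark other than the composite is named for it.

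**Conclusion.** The point holds in conditional form. As worded, objective 1 calls for an accuracy estimate that will be inflated if the clinical score contains any cardinal-sign item and is judged against the WHO composite. Under the assumptions above, uninformative signs alone give an AUC of about 0.83 to 1.00, or about 0.69 to 0.80 with three noise items added, against 0.50 for true disease. The 100% specificity belongs only to the illustrative rule applied to the same examination.

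It would be wrong to read this as a flaw in the main result. PCR and ultrasound are explicitly kept out of the reference, so the primary PCR accuracy is untouched, as is the prognostic part of objective 1. It is also no fault that a clinical composite contains clinical signs. The defect is that one objective lists the clinical score as a test to be judged against it. It is worth correcting before the analysis planned from February 2027.

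**What to change.** Reword objective 1 so that diagnostic accuracy is estimated for the molecular and ultrasound scores only. Use the clinical findings descriptively, for the comparison with ultrasound that objective 2 already sets out, and for prognosis.

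If a diagnostic clinical score is kept, build it only from items that are neither components of the composite nor dependent on a leprosy diagnosis, for example contact history and duration of symptoms. Sensory loss in lesions, nerve thickening, sensory and motor deficit and the smear result would be left out, as would the operational and Ridley-Jopling classes.

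The change costs a few words in one objective and needs no new patients, data or procedures. The downside is that the study will report no accuracy figure for the clinical examination itself.

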## Methods

### Study Design and Population Studied

This is a diagnostic study with prospective collection. Patients aged 14 years or older will be enrolled after agreeing to and signing the informed consent form. The informed consent form will be signed by the responsible adult in the case of participants under 18 years of age. This research is in line with the Declaration of Helsinki and its revision made in 2013.

The case definition will be determined by a professional external to the investigation according to the standard procedures of the leprosy outpatient clinic of the UHB, which consist of clinical history, general physical examination, and dermato-neurological examination. Case definition will follow the World Health Organization (WHO) composite reference standard for the diagnosis of leprosy [32]. Direct investigation of the bacillus will be performed via SSSs of lesions, earlobes, and elbows. After the procedure, collected material from perineural aspiration and dermal lesions will be sent to the laboratory within a maximum period of 24 hours. The results of the perineural aspiration will only be known to researchers by the end of the study. Morphological data described in the ultrasound examination will be accessed by a blinded ultrasound specialist based on deidentified ultrasound images.

Clinical and molecular examinations will be performed, and their results will be compared to the sonographic findings, which will be collected monthly for 1 year. Molecular findings will be compared to the composite reference standard. Patients will be evaluated clinically, via ultrasound, and molecularly immediately after clinical diagnosis and 1 year after the start of treatment.

